**Figure 4 Fig4:**
[figure not shown]
**Experimental set-up in the Ifakara Tunnel Test (ITT).** Ifakara Tunnel situated at Bagamoyo Research Training Centre (BRTC) in Kingani, Bagamoyo. The tunnel is a 50 m long, 3 m wide and 2.1 m high steel tube frame construction upon a concrete base surrounded by a water channel and beneath a beamed wooden frame supporting a corrugated steel roof **(A)**. Net covered tunnel divided into 10 individual compartments containing bed and adjustable steel net frame **(B)**. Experimental set up for Ifakara Tunnel Test. A human volunteer will sleep beneath the LLIN from 21.00 hrs to 06.00 hrs. *Anopheles gambiae* mosquitoes will be released from the holding cages by raising a cage from its wooden base (arrow) using a nylon string **(C)**. At the end of the experiment, all mosquitoes within each of the compartments will be removed with a Prokopack **(D)**.

Each of the ten experimental compartments will be provided with a steel bed frame and foam mattress upon which a volunteer will sleep during each test and over which the LLIN will be draped (Figure 4C). A human volunteer will sleep beneath the LLIN from 21.00 hrs to 06.00 hrs to represent user conditions. For each test, 30 nulliparous 2-8 day old, disease-free *An. gambiae* s.s. mosquitoes will be introduced. At 06.00 hrs, the mosquitoes within the compartment will be collected using a mechanical aspirator (Prokopack; [39]) and scored for knockdown (KD), 24-hour mortality and blood-feeding success.

All participants in ITT experiments will be male staff members of IHI who have received appropriate training and are experienced in conducting semi-field tunnel tests. All participants will be recruited on written informed consent, which explains the risks and benefits of the study and are free to leave the study without explanation. The risk of disease transmission to volunteers is very low.

#### Chemical residue (C Component)

After biological efficacy and physical degradation testing in semi-field facilities in Bagamoyo has taken place, the same 48 LLINs per product will be used for chemical residue analysis. Chemical residues will be determined by HPLC [40]. The HPLC analysis will be carried out in a WHO Collaborating Centre for Quality Control of Pesticides (Walloon Agricultural Research Centre; CRA-W) following the latest WHO recommendations. Four sub-samples of 30 cm x 30 cm will be taken from each net representing the entire net. Samples will be kept at 4°C in aluminium foil until analysed to determine the total content of permethrin (Olyset^®^) or deltamethrin (Netprotect^®^ and PermaNet^®^2.0) in g/kg.

#### Resistance monitoring (R Component)

The resistance monitoring component builds upon the existing nationwide longitudinal monitoring of insecticide resistance in Tanzania that has already been carried out in 26 selected sentinel districts from different ecological zones of Tanzania [41]. In the current study, insecticide resistance will be assessed in a total of 15 districts (Figure 2). Eight of these districts coincide with the ABCD part of the project. Insecticide resistance will be monitored in cross-sectional countrywide surveys conducted annually throughout the project life. These surveys will be carried out in May/June, just after the long rainy season. The susceptibility levels and resistance mechanisms of malaria vectors to insecticides of public health and agricultural relevance in Tanzania will be determined. Results will feed into the online geospatial application IR Mapper [23]. *Anopheles* larvae will be collected in easily accessible larval habitats in one or two villages per district. Each breeding site will be geo-referenced using GPS. Larvae will be bred to adult mosquitoes in field laboratories, which will be maintained on 10% glucose solution in mosquito cages. Three- to five-day old F1 generation mosquitoes will be tested using standard WHO insecticide susceptibility testing procedures [42]. Mosquitoes will be exposed to papers impregnated with the WHO-recommended discriminating concentrations (v⁄w) of 0.05% deltamethrin, 0.05% lambda-cyhalothrin, 0.75% permethrin, 0.1% bendiocarb, 1% fenitrothion and 4% DDT prepared at University Sains, Malaysia [42]. During exposure, KD rates will be recorded after a range of exposure times. Mosquitoes will then be provided access to 10% glucose solution and 24 hour mortality will be scored. All mosquitoes will be identified using keys described by Gillies [43, 44] and *An. gambiae* sibling species identified using established Polymerase Chain Reaction (PCR)-based methods [45]. PCR-based standard methods will also be used to detect kdr mutations [46] and biochemical assays will be used to detect the enzyme-based resistance mechanisms in mosquitoes.

### Statistics and data analysis

#### Sample size calculation

Sample size calculations were based on the primary outcome measure of net attrition using the standard formula for the difference between two proportions [47]. The BCD components were treated as an additional sub-sample to the original calculated sample size. Assuming an average of 3 nets per household and a coefficient of variation of 0.25, then the formula on page 110 of Hayes & Moulton [48] gives a sample size of 973 households per arm to detect a difference in attrition between two brands with attrition rates of 47.5% and 52.5% with 90% power. Therefore, there will be at least 90% power to detect a 5% difference in attrition rates. Loss to follow up and households excluded due to sub-sampling have been added to the final sample size to give (1,140 households * 3 nets/ household) = 3,420 LLINs per LLIN product (Table 3).

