#### Prospective study

Attrition, net use and user behaviour (Additional file 2), and physical degradation of study nets will be assessed in every consenting household at three subsequent sampling points (10, 22, and 36 months) after the initial LLIN distribution. All households will be surveyed for attrition and a sub-sample of three nets per household will be assessed for physical degradation. Field interviewers will be trained using an amended version of a recently developed USAID/NetWorks-supported training tool kit to assess the number of different category sized holes under field conditions [33].

At each time point, all nets from 48 randomly selected households for each net product will be taken for sub-sampling to validate the D component (physical degradation) assessment in the laboratory, and for B (biological efficacy against mosquitoes) and C (HPLC analysis) components efficacy testing (Figure 1). These households will be randomly selected stratified by district and LLIN product so that six nets from each district per product are evaluated for BCD components. All sampled nets will be replaced with new nets of the same kind except for Netprotect^®^ nets which will be replaced by Olyset^®^, and the sampled household will be excluded from subsequent sampling rounds.

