#### Data analysis

We will collect a set of response variables (Table 1) and explanatory variables. The explanatory variables will be collected from household questionnaires and observations and will include time after net distribution, net product, geographical location, patterns of net use (e.g. type of bed, frequency of net use), net status, washing and handling, perceptions of nets and socioeconomic status of the household. All response variables will be analysed using the statistical programs STATA^®^13 (http://www.stata.com/) and R (http://www.R-project.org/). Regression modelling including multivariate generalised linear models and generalised linear mixed models will be used to determine covariates affecting net durability components such as LLIN age, geographical location and data collected from household surveys. Principal Component Analysis (PCA) will be used to determine a combination of variables for socioeconomic status to explain the overall observed variation and reduce the complexity of the data. In order to analyse net attrition and physical degradation in more detail, 95% confidence intervals will be calculated for the attrition and ‘unserviceable’ physical condition of each net product at the three prospective time points. At each point, logistic regression with a category for each brand of net will be performed to assess if there is a difference in attrition between the three net products. If a significant difference is found, then pairwise comparisons will be examined.

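### The 973 households per arm do not follow from the printed inputs, which give 832 at two-sided 5%, so the margin for loss to follow-up cannot be determined

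*Protocol article*

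**What the plan says.** The Sample size calculation section of the protocol article sizes the study on attrition: "Sample size calculations were based on the primary outcome measure of net attrition using the standard formula for the difference between two proportions". The inputs are "Assuming an average of 3 nets per household and a coefficient of variation of 0.25", and "two brands with attrition rates of 47.5% and 52.5% with 90% power". By a cluster-trial formula cited to a textbook page, this "gives a sample size of 973 households per arm to detect a difference in attrition between two brands". The section concludes that power is at least 90% for a 5% difference. It gives no significance level.

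It then says "Loss to follow up and households excluded due to sub-sampling have been added to the final sample size", which brings the figure to 1,140 households per product. It gives no loss rate.

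The Prospective study section describes what sub-sampling removes. At each of months 10, 22 and 36, all nets are taken from 48 households per product, and "the sampled household will be excluded from subsequent sampling rounds".

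**The concern.** The article prints the inputs, names the formula and prints the answer, so the answer can be checked. It does not come out: 973 is 17% above what the inputs give. Either a printed input is not the one used, or 973 is wrong, or a setting was used that the text does not disclose.

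This matters because 973 is the base to which the allowance for loss and sub-sampling was added. If the true requirement is 832, the study can lose about a fifth of the households still available at month 36 and keep 90% power. If it is 973, it can lose only about one in fifteen. The two cases carry different assumptions about household clustering or household size, and the text does not show which one applies.

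**Working it through.** **Inputs**
- Nets per household m = 3, CV k = 0.25, p0 = 0.475, p1 = 0.525, power 90% (Sample size calculation).
- Two-sided alpha of 5%: an assumption. It agrees with the Data analysis section, where "95% confidence intervals will be calculated for the attrition".
- 1,140 households per product enrolled; 48 per product removed at each round (Table 3; Prospective study).

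**Formula** (unmatched clusters, two proportions)

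c = 1 + (z_α/2 + z_β)² × [p0(1−p0)/m + p1(1−p1)/m + k²(p0² + p1²)] / (p0 − p1)²

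**Attempt to reproduce 973**
- (1.960 + 1.2816)² = 10.507
- Binomial terms: 2 × 0.475 × 0.525 / 3 = 0.16625
- Between-household term: 0.0625 × (0.2256 + 0.2756) = 0.03133
- Sum: 0.19758
- c = 1 + 10.507 × 0.19758 / 0.0025 = 831.4, so **832**
- 973 / 832 = 1.17

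**Variants**

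| Change from the base case | Households per arm |
|---|---|
| Pair-matched version (+2 instead of +1) | 833 |
| One-sided 5% | 678 |
| Continuity correction | about 848 |
| 95% power | 1,028 |
| Two-sided alpha 0.05/3 (three pairs) | 1,069 |
| Two-sided alpha 0.025 | 982 |
| k = 0.36 | 973 |
| m = 2.5 | 972 |

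The last three come close to 973, and none of those settings appears in the article.

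**Power on the printed inputs:** 93.9% with 973 households per arm and 95.3% with 1,044.

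**Room for loss.** Households sampled at months 10 and 22 are gone before the month-36 survey: 1,140 − 2 × 48 = 1,044.

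| Round | Available | Allowable loss if 973 needed | Allowable loss if 832 needed |
|---|---|---|---|
| Month 10 | 1,140 | 167 (14.6%) | 308 (27.0%) |
| Month 22 | 1,092 | 119 (10.9%) | 260 (23.8%) |
| Month 36 | 1,044 | 71 (6.8%) | 212 (20.3%) |

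**Power at month 36 with 20% loss** (0.8 × 1,044 ≈ 835 households): 90% with k = 0.25 and m = 3; about 85% with k = 0.36, or with m = 2.5.

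**The case against.** Four points can be made for the plan.

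1. *Alpha is not printed.* The figure of 832 therefore rests on a supplied convention, and a two-sided 2.5% level gives 982, within 1% of 973. This stands as a limit on how the point is worded. Nothing in the article supports a 2.5% level, however, and correction for all three pairwise comparisons would give 1,069.

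2. *Both printed inputs may be right.* Three nets is an average, and households receive nets according to their sleeping spaces. If size varies, the binomial term depends on the harmonic mean, which lies below 3. An illustrative mix of 1, 2, 2, 3, 3, 3, 3, 4, 4 and 5 nets has mean 3 and harmonic mean 2.48, and gives about 978. This is a plausible origin for 973, so the defect may be an unexplained step and not a wrong input. The article does not describe such a step.

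3. *The discrepancy is in the safe direction.* On the printed inputs, 973 gives more than 90% power, so the claim of at least 90% holds. A reader might infer that the study is underpowered; the documents do not support that.

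4. *The power claim is tied to no time point.* A reader might take it as a promise for month 36 in particular, but the section does not say so, and the analysis tests brands at each of three rounds. The 6.8% is the tightest of the three allowances and applies only if 973 is needed. With no stated loss rate, nothing shows it to be inadequate.

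One further uncertainty concerns the sub-sample. The Figure 1 legend speaks of 48 nets per product, whereas the Prospective study section speaks of all nets from 48 households. If only 16 households left per round, 1,108 would remain and the allowance against 973 would be 135 / 1,108 = 12.2%. The Prospective study text is explicit about households, so 1,044 is used here.

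**Conclusion.** The concern holds as a failure to reproduce. The printed inputs give 832 households per arm at an assumed two-sided 5%, not 973, and no setting found in the article closes the 17% gap. The article cannot show whether the CV, the effective household size, an undisclosed alpha or the 973 itself is responsible.

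The consequence is conditional. If the printed inputs are right, the plan is more generous than it claims. If 973 reflects a larger CV or a smaller effective household size, 90% power at month 36 survives only 6.8% loss after sub-sampling, and 20% loss would bring it to about 85%. The correction should be made because this is the only sample size justification for the primary outcome, but it does not show that the study is too small.

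**What to change.** In the Sample size calculation section:
- State alpha and whether the test is two-sided.
- Either replace 973 with 832, or keep 973 and print what produced it (for example, the CV used or the effective net count per household).
- State the loss rate assumed in going from that figure to 1,140.
- Give power and allowable loss for the month-36 round after the 96 sub-sampled households per product are removed: 20.3% if 832 is the requirement, 6.8% if 973 is.

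The cost is one recalculation and a few reworded sentences. Enrolment and field procedures stay as they are. The stated loss allowance may turn out less favourable than readers would now assume.

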#### Data analysis

We will collect a set of response variables (Table 1) and explanatory variables. The explanatory variables will be collected from household questionnaires and observations and will include time after net distribution, net product, geographical location, patterns of net use (e.g. type of bed, frequency of net use), net status, washing and handling, perceptions of nets and socioeconomic status of the household. All response variables will be analysed using the statistical programs STATA^®^13 (http://www.stata.com/) and R (http://www.R-project.org/). Regression modelling including multivariate generalised linear models and generalised linear mixed models will be used to determine covariates affecting net durability components such as LLIN age, geographical location and data collected from household surveys. Principal Component Analysis (PCA) will be used to determine a combination of variables for socioeconomic status to explain the overall observed variation and reduce the complexity of the data. In order to analyse net attrition and physical degradation in more detail, 95% confidence intervals will be calculated for the attrition and ‘unserviceable’ physical condition of each net product at the three prospective time points. At each point, logistic regression with a category for each brand of net will be performed to assess if there is a difference in attrition between the three net products. If a significant difference is found, then pairwise comparisons will be examined.

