## Background

The recent successes in malaria control in sub-Saharan Africa (SSA), specifically in Tanzania where malaria deaths have reduced by 70% since 2003, has been largely attributable to the massive scale up of vector control tools, particularly Long Lasting Insecticidal Nets (LLINs) [1–3]. However, sustained malaria control is costly, and dependent on continuing political and donor support. As political commitment diminishes, the deliveries of life-saving control tools will slow down and risk the reversal of the huge achievements to date. Global commitments for malaria control in 2012 were approximately US$2.5 billion, far below the estimated sum of US$5.1 billion required for the task [4]. Global funding mechanisms are projected to decelerate even further in the coming years, leaving gaps of US$2.25 billion before achieving universal access to malaria interventions [1]. Therefore, maximising the impact of interventions through selection of the most cost effective and long lasting interventions is a health policy priority.

Despite the huge financial and logistical investments in the development, production and distribution of LLINs worldwide, there are still limited data available on the LLIN durability under user conditions. The World Health Organization (WHO) released specific guidance on LLIN durability monitoring [5, 6], which was incorporated into guidelines for laboratory and field-testing of LLINs [7] to support national governments with the design of standardised net monitoring and evaluation studies. Effective net life has been estimated to be 3-5 years [8], but some studies indicate that LLIN brands may last less than three years under operational conditions [9–12]. It is only recently that researchers have started to investigate net attrition, i.e. how long nets remain in use in a household, and constructed net survivorship curves [5, 13]. Durability of mosquito nets should thus be defined and measured by the whole process of net loss – from attrition and physical damage to the chemical loss of insecticide residue [5].

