**Table 1 Tab1:** **LLIN durability components**

Component	Definition	Response variables for analysis
**A**ttrition	Net loss from household through discarding or use for alternative purpose	- Net presence.
**B**iological efficacy	Ability of net to incapacitate or kill anopheline mosquitoes after contact with insecticide	- Mosquito knockdown (%) 60 minutes post-exposure.
		- Mosquito mortality (%) 24 hours post-exposure.
		- Percentage of bloodfed mosquitoes.
**C**hemical residue	Amount of active ingredient in fibres	- Proportion of nets with active ingredient equal to WHO standard g/kg
**P**hysical degradation	Physical state of the net defined through number, size and location of holes to estimate protection against mosquito bites	- Proportionate Hole Index (pHI) / hole area by location on net.
		- Proportion of nets with a pHI exceeding ≥643 [6].

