### ABCDR components

#### Attrition (A component)

Attrition of LLINs is defined as the proportion of LLINs that are no longer in use as mosquito nets to sleep under in the receiving household after a given amount of time. This is commonly due to loss through nets being damaged, discarded, or used for other purposes than sleeping under. Nets that are sold, given away or stolen will be excluded from the attrition analysis following WHO guidelines [6] as they may still be “serviceable”.

Trained field interviewers will perform the field visits of all households selected from the master list and voluntarily participating in the study during the sampling points (retrospective sampling, 10, 22 and 36 months after prospective LLIN distribution). Questionnaire data will be collected using Open Data Kit (ODK) Collect software (http://opendatakit.org/use/collect/) on Android tablet computers (Google Nexus One). Observations by the field workers on presence and absence of distributed nets, the location of the net (hanging or stored away), fabric integrity and the net condition are included in the questionnaire (Additional file 2).

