#### Physical degradation (D component)

The physical degradation, or integrity, of the nets will be measured by counting the number, location and size of hole(s) in each net. The proportional hole index (pHI) will be calculated using the hole size categories as per WHO guidelines [5, 6] (Table 4). In addition to the different category sized holes, we will also include five different hole locations on the net by dividing the side panels of the net into a total of four zones from top to bottom, each measuring 37.5 cm, and counting holes in the roof separately as a fifth location (Figure 3). Mosquitoes are more likely to aggregate around certain locations on occupied bed nets (e.g. the roof; [34]). In addition, the lower edges of the bed nets are more likely to be severely damaged, but they are also more likely to be tucked in at night, potentially avoiding mosquito entry [35]. By counting the holes by location, we will be able to take into account these factors when analysing the hole index data and give different weights to holes in different locations. To our knowledge, this formula has not yet been developed. One of our aims is therefore to incorporate hole location into the equation, and to compare its relative importance to a simpler model in terms of protection against mosquitoes in semi-field experiments. Holes will be counted both in the laboratory and in the field using a collapsible metal frame made out of locally available economical materials (Figure 3). In the field, holes in a maximum of three prospective nets will be counted per household due to logistical and time constraints.

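### The 'unserviceable' proportion is measurable only in nets that survive, attrition ignores damage in nets still in use, and no listed outcome combines the two

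*Protocol article*

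**What the plan says.** Table 1 lists the response variables by component. Attrition is represented by net presence. Physical degradation is represented by the proportionate hole index (pHI) and by "Proportion of nets with a pHI exceeding ≥643". No listed variable joins the two.

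The Data analysis section then plans 95% confidence intervals for attrition and for the 'unserviceable' "physical condition of each net product at the three prospective time points". The only test between products that it names is for attrition: at each visit, "logistic regression with a category for each brand of net will be performed to assess if there is a difference in attrition", followed by pairwise comparisons if the result is significant. Regression models for the durability components are also described in general terms, with net product among the explanatory variables.

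On measurement, the Prospective study section says: "All households will be surveyed for attrition and a sub-sample of three nets per household will be assessed for physical degradation". The Physical degradation section repeats the cap on field counts: "holes in a maximum of three prospective nets will be counted per household due to logistical and time constraints".

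On the link between damage and loss, the Attrition section defines attrition as nets no longer used for sleeping under in the receiving household and adds: "This is commonly due to loss through nets being damaged, discarded, or used for other purposes than sleeping under". Nets sold, given away or stolen are left out of the attrition analysis.

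On the aim, the Background says: "Durability of mosquito nets should thus be defined and measured by the whole process of net loss". It also promises an assessment of effective life over three years. The Discussion equates the life of a net with how long it protects effectively, and wants the results to guide procurement and the timing of replacement.

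**The concern.** A net contributes a hole count only if it is there to be examined. By the article's own account, nets often leave the household because they are damaged. The denominator of the unserviceable proportion is therefore selected on the property being measured. Randomisation protects a comparison of all distributed nets. It does not protect a comparison of the nets that households chose to keep. Discard behaviour could differ by product, since the nets differ in polymer and denier and the article concedes that they may be physically distinguishable.

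Attrition has the opposite gap: a net torn past the pHI threshold but still slept under counts as retained. The two proportions can therefore point in opposite directions for the same product, and the article gives no summary that resolves the disagreement. The programme wants to know which product leaves most households with a net that still protects, and neither proportion answers that.

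**Working it through.** The plan gives no figure for degradation, so there is none to reproduce. Its sample size concerns attrition only and does not enter here. The documents give no tearing or discard rates, so every rate below is an assumption chosen to show a range. 'Unserviceable' is taken to mean pHI at or above 643, the only threshold in Table 1.

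**Notation.** T = share of nets that become unserviceable; d = share of those that are discarded; h = share of the other nets that are lost.

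- Attrition = T·d + (1 − T)·h
- Unserviceable among surviving nets = T(1 − d) / (1 − attrition)
- Combined failure (lost or unserviceable) = attrition + T(1 − d) = T + (1 − T)·h

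The last expression does not contain d. With equal T and h, the discarding of torn nets moves both planned proportions but leaves the combined outcome unchanged.

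**Equal tearing, large difference in discarding** (T = 50%, h = 5%; d = 60% for product A, 20% for product B):

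| | A | B |
|---|---|---|
| Torn and kept | 0.5 × 0.4 = 0.200 | 0.5 × 0.8 = 0.400 |
| Intact and kept | 0.5 × 0.95 = 0.475 | 0.475 |
| Surviving | 0.675 | 0.875 |
| Attrition | 32.5% | 12.5% |
| Unserviceable among survivors | 0.200/0.675 = 29.6% | 0.400/0.875 = 45.7% |
| In use and serviceable, of distributed | 47.5% | 47.5% |

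The unserviceable proportion favours A by 16 points and attrition favours B by 20, yet the products serve households equally well.

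**Equal tearing, small difference in discarding** (T = 50%, h = 5%; d = 45% vs 35%): 0.275/0.750 = 36.7% vs 0.325/0.800 = 40.6%, a gap of about 4 points. The share in use and serviceable is again 47.5% in both.

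**Range** with h = 10%, T from 30% to 50%, and d pairs 20/60, 30/50 and 40/60: the gap among survivors runs from about 6 points (T = 30%, d = 30% vs 50%: 25.0% vs 19.2%) to about 16 points (T = 50%, d = 20% vs 60%: 47.1% vs 30.8%). Combined failure is identical within each pair.

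**Unequal tearing** (h = 10%):

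- Survivor pHI can reverse the order. Product C has T = 40%, d = 20%; product D has T = 50%, d = 60%. Unserviceable among survivors is 0.32/0.86 = 37.2% vs 0.20/0.65 = 30.8%, so D looks more intact. Combined failure is 46% vs 55%, so C is better.
- Attrition can also reverse it. Product E has T = 50%, d = 20%; product F has T = 40%, d = 60%. Attrition is 15% vs 30%, which favours E. Combined failure is 55% vs 46%, so F is better.

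**The case against.** Four points can be made for the plan.

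First, the article condenses a fuller plan, and nothing in Table 1 forbids deriving a combined measure. That is fair as far as it goes. But the article does list its response variables for analysis, and the list falls short of the definition of durability that the same article adopts.

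Second, both proportions are reported together, per product and per visit, and attrition is primary, so a product whose torn nets are thrown out early is penalised there. This stands. A reader might infer that products will be formally tested on surviving-net pHI alone, or that procurement will follow one measure in isolation. The documents do not say so: the only named test is for attrition, and for unserviceable condition the article specifies confidence intervals plus general regression models. That holes are counted only in surviving nets is itself an inference from how counting works; the article does not put it in words.

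Third, when denominators align, the combined point estimate is the product of the two planned quantities: 0.675 × (1 − 0.296) = 0.475 and 0.875 × (1 − 0.457) = 0.475. So the information is not lost. But multiplying two published proportions supplies neither an interval nor a comparison of products. The denominators also do not fully align, because attrition covers all nets and hole counts cover at most three per household.

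Fourth, a threefold difference in discarding is a strong assumption for white nets of the same shape and size, randomised between households within villages and partly blinded. This stands as a limit on the size claimed, though not on the mechanism.

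**Conclusion.** The structural point holds. As listed, the unserviceable proportion conditions on survival, attrition disregards damage in nets still in use, and no response variable measures the whole course of loss that the article sets out to measure. With equal tearing, the spurious gap in the unserviceable proportion is about 4 to 16 points under the assumed rates. For scale, the trial is sized to detect a 5-point difference in attrition, so the lower end of the range is below that difference and the upper end well above it.

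The documents support no estimate of the actual distortion, and it would vanish if torn nets were discarded at the same rate in every product with equal tearing. It would be too strong to conclude that the products will be ranked wrongly: the plan shows both measures side by side and sets no rule that ranks on either one. Nor does the article say that the three nets for hole counting are picked selectively; it leaves their selection open. The change should be made, because it supplies the quantity the trial is meant to deliver from data already gathered.

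**What to change.** Add to Table 1 and to the Data analysis section a combined outcome per distributed net: still in use as a mosquito net in the receiving household, as the Attrition section defines it, and pHI below 643. The in-use wording matters because Table 1 records only net presence, and a repurposed net may still be present.

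- **Denominator:** all distributed nets, leaving out those sold, given away or stolen, as for attrition, with a sensitivity analysis for that exclusion because it too arises after randomisation. Leave out households already removed by earlier sub-sampling.
- **Comparison:** products at each visit, with a model that allows for household clustering. The article already names generalised linear mixed models.
- **Reporting:** attrition and the unserviceable proportion beside the combined outcome, with pHI among surviving nets labelled descriptive.
- **Hole counting:** where a household has more than three nets, choose the three at random and weight for the sampling fraction. Random choice alone would under-represent nets from larger households.

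The cost is a small amount of extra analysis. Presence, use and hole counts are already recorded at each survey, and every net carries a serial number. At submission only the 10-month survey was complete, so the selection rule could still apply at 22 and 36 months.
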